## Eligibility Criteria

### Inclusion Criteria

The participant must meet all the inclusion criteria to eligible for this study:

1. Be 16-29 years old.
2. Being competent and willing to consent to study participation.
3. Meets CHR criteria for a psychosis risk syndrome based on the Structured Interview for Psychosis Risk Syndromes (SIPS) within the past 3 years.

### Exclusion Criteria

An individual who meets any of the following criteria will be excluded from participation in this study:

1. Diagnostic and Statistical Manual of Mental Disorders (DSM-5) diagnosis of psychotic disorder (e.g., schizophrenia spectrum disorder, mood disorder with psychotic features)
2. Diagnosis of intellectual disability
3. Severe developmental disorder
4. Acute suicidality requiring immediate life-saving intervention (i.e., inpatient psychiatric care).
5. Receiving any additional psychotherapy interventions or structured digital mental health support during the study period.

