Research personnel will contact participants according to their preferred mode of communication (email, telephone, SMS text), which will be recorded in the pre-screening/subject log. In the case of text messaging, personnel will only contact participants to schedule or remind participants of upcoming appointments.

All patients will be given the option to participate. Participation in the study is voluntary. The decision to participate will not affect patients’ receipt of treatment or clinical services. Participants will be informed that they have the option of terminating their participation at any time, without consequence and that no new data will be collected on them.

Participants will be recruited through the Slaight Centre for Youth in Transition’s centralized recruitment process. All subjects will be pre-screened with the Slaight REB approved “pre-screen form” that is implemented across all SFCYT studies to allow for alignment and data sharing and recruitment; this data will be entered into a password protected and restricted pre-screen tracking database. We conduct case review meetings twice a week to review recruitment and to identify new patients who may be eligible for research studies. Our centralized recruitment strategy allows us to ‘triage’ and ‘group’ participants into non-competing research studies to encourage referrals among PIs.

Recruitment will also be enhanced by the Toronto Adolescent and Youth (TAY) Cohort study (PI; [name]) that is recruiting 3000 youth, and emerging adults, aged 11-24 years over 5-years. The TAY study offers rich phenotypic data and aims to investigate mechanisms of disease in young people presenting to mental health services. We expect to identify many individuals with CHR from the TAY Cohort study, where to date almost 50% of participants demonstrate clinically significant levels of psychosis spectrum symptoms.

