## Participant Withdrawal Criteria

Participants are advised in the consent form that they are free to withdraw from the study at any time without prejudice and may be withdrawn at the Investigators discretion.

The study participation will also be terminated should participants develop or are found to have any condition that might compromise safety (e.g., unstable vitals). Other reasons for withdrawing individual participants from the study may include one of the following:

- Major protocol violation
- Participant lost to follow-up.
- Withdrawal of consent
- Any participant may be discontinued from the study at the discretion of the investigators if it is deemed to be in the best interest of the participant.

The reason for participant discontinuation or withdrawal from the study will be recorded within the participant’s research record, and/or legal health record.

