**Control Group Procedures**

Participants in the control group will continue to receive treatment as usual, which may consist of routine appointments with healthcare providers, medication management, and other supportive services as deemed necessary by their care team. Outcome measures will be collected at study entry and at 8-weeks for participants in the treatment as usual group.

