## Concomitant Therapy

Patients participating in this study will continue to be eligible for and continue their standard care, which comprises an outpatient multidisciplinary team approach including, psychiatric follow up and potential medication management. Concomitant medication/therapies will be verified with research participants at each visit. Concomitant medication analysis will be conducted using multivariate analysis to control possible effects. Receiving any additional psychotherapy interventions or structured digital mental health support during the study period is an exclusion criterion for the study.

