## Statistical Methods

Data will be analyzed principally using descriptive statistics to assess rates of recruitment, retention, intervention fidelity, engagement, and treatment response. Distributional characteristics of the outcome measures will be assessed for ceiling and floor effects and rates and patterns of missing values. Exploratory trial outcomes including impact of d-DBT on emotional regulation, psychiatric symptoms and functioning will be analyzed using (generalized) linear mixed-effects models with time (baseline, post-treatment), group (d-DBT vs control), time by treatment interaction as the primary predictor. The model will also include covariates to account for pre-treatment clinical characteristics and/or key demographics. The model form will be determined by the distribution features of the outcomes of interest (e.g, continuous, binary or count-type). The efficacy outcome will be impact of d-DBT on functioning, via the Global Functioning: Social and Role Scales. Our prior work with youth has informed us that functioning is more relevant to them than symptom severity (91). Given the small sample size, appropriate to a feasibility trial, we will also calculate point and confidence estimate of effect sizes (Cohen’s *d*) Effect sizes will help with the estimation of the sample size needed for a larger scale confirmatory randomized control trial in the future. Both ITT analysis and per-protocol/completers-only analysis will be conducted to gain insight of estimated efficacy of different subgroups of participants. Full information maximum likelihood approach will be adopted to deal with missing data under the missing-at-random assumption. Diagnostic analysis will be conducted to evaluate the soundness of the statistical assumptions carried by the methods. While the analytic approach can be seen as too complex for the small sample size, it will offer guidance for the analysis plan of the full-scaled trial.

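### Exclusion criterion 5 depends on therapy received during the study, so read literally it permits withdrawal of randomised participants and puts the ITT analysis at risk

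*Protocol*

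**What the plan says.** Exclusion Criteria opens with "An individual who meets any of the following criteria will be excluded from participation in this study". Criterion 5 on that list is "Receiving any additional psychotherapy interventions or structured digital mental health support during the study period". Concomitant Therapy repeats it: "Receiving any additional psychotherapy interventions or structured digital mental health support during the study period is an exclusion criterion for the study". The same section says that concomitant medication and therapies are checked with participants at every visit.

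On timing, the Schedule of Events marks the inclusion/exclusion determination in the Screening column only. Participant Recruitment and Screening places the assessment after consent, but also allows chart review to inform eligibility on a continuing basis.

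Participant Withdrawal Criteria concerns leaving the study as a whole. Its possible reasons include "Major protocol violation" and investigator discretion. Newly received psychotherapy is not named, and stopping d-DBT is not distinguished from leaving follow-up.

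Control Group Procedures lets control participants receive "other supportive services as deemed necessary by their care team". Statistical Methods states that "Both ITT analysis and per-protocol/completers-only analysis will be conducted", with full information maximum likelihood under missing-at-random. Outcomes are measured at study entry and at 8 weeks.

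**The concern.** The other exclusion criteria describe a state that can be established at entry. Criterion 5 describes something that may happen after randomisation, and the text attaches exclusion from participation to it. A site applying it as written could treat a participant who receives other support at week 4 as no longer eligible and withdraw that person from the study.

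The event is plausible under the protocol's own terms. Usual care is open-ended, and Risks/Benefits asks the team to identify participants who need treatment and help them obtain it. Staff could therefore help someone into care that meets an exclusion criterion. Need for extra help plausibly tracks poor outcome, and its frequency may differ between arms. Removal on that basis would be a post-randomisation selection related to outcome.

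Two results are exposed: the between-group effect size, which Statistical Methods intends to use in planning a larger trial, and retention, which is a primary feasibility outcome.

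**Working it through.** **1. The sections side by side (protocol).**

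| Section | Bearing on a randomised participant who receives other support |
|---|---|
| Exclusion Criteria, item 5 | Meets a criterion for exclusion from participation; no time point given |
| Concomitant Therapy | Repeats the criterion; therapies checked at each visit |
| Schedule of Events | Eligibility determined at screening only |
| Participant Recruitment and Screening | Eligibility may be informed on a continuing basis |
| Participant Withdrawal Criteria | Major violation or discretion permits withdrawal from the study |
| Control Group Procedures | Open-ended supportive services; no line drawn against the excluded support |
| Statistical Methods | ITT and per-protocol/completers analyses, neither defined |

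The literal route to removal is open but not mandatory. The screening-only reading is also available. The sections do not settle which applies.

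**2. Retention.** Inputs: 60 participants (Overall Design), 80% retention (Specific Aim 2), about 20% dropout (Sample Size and Power).
- Target: 0.80 × 60 = 48 retained.
- Expected: 60 − 0.20 × 60 = 48 retained, so there is no slack.
- Each further removal costs 1/60 = 1.7 points; one gives 47/60 = 78.3%.

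**3. Precision.** The plan's own figures first, assuming two-sided 5% and 80% power for the effect size:
- Margin: 1.96 × √(2/24) = 0.57 SD, as stated, on 24 per arm after dropout.
- Detectable effect: (1.96 + 0.84) × √(2/30) = 0.72, as stated, on 30 per arm. (At 24 per arm it would be 0.81. That difference does not bear on this point.)

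Margin with further removal on top of 20% dropout (removal rates are assumptions; the documents give none):

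| Removed | Control arm only | Both arms |
|---|---|---|
| 10% | ±0.58 | ±0.60 |
| 20% | ±0.60 | ±0.63 |
| 30% | ±0.62 | ±0.68 |

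The loss of precision is modest.

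**4. Possible bias.** All inputs here are assumptions.
- Extreme case: the worst-functioning fraction x of controls is removed, no one is removed from d-DBT, and raw means of those remaining are compared. The control mean rises by φ(z_x)/(1 − x), which is 0.195 SD at x = 10% and 0.350 SD at x = 20%. If need for therapy correlates 0.5 with outcome, these halve to 0.10 and 0.17 SD.
- Milder case: those removed differ from the rest of their arm by s SD, so the mean of those retained shifts by x × s. This runs from 0.10 × 0.3 = 0.03 SD to 0.30 × 0.8 = 0.24 SD.

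Removing poorly functioning controls raises the control mean, so the bias would run against d-DBT. Removal from the d-DBT arm would push the other way.

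**5. Missing data.** There is no outcome assessment between baseline and week 8. For someone removed in between, the likelihood model has the baseline values and covariates but no record of the change that led to the extra support. Missing-at-random is least secure for exactly these participants.

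**The case against.** A reader might infer that the criterion defeats or contradicts the ITT analysis. The documents do not support that. No section orders removal of a participant who receives other support, calls such a person a major violator, or drops anyone from an analysis set. Leaving participation is not the same as leaving the ITT set: full information maximum likelihood can retain anyone with baseline data, and a per-protocol analysis is a natural place to deal with other therapy.

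A reader might also infer that week-8 data are necessarily lost, from the statement that "no new data will be collected on them". That sentence concerns participants who choose to end their own participation. It does not cover withdrawal by the investigator, on which the protocol is silent. Those who choose to withdraw may still be invited to interview (Qualitative methods).

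Three further points stand. The screening-only entry in the Schedule of Events supports reading criterion 5 as therapy ongoing or planned at entry. Concomitant therapies are already verified at each visit, so most of the recording needed exists. Control Group Procedures does not name psychotherapy or structured digital support, so it is an unclear boundary and not a direct conflict.

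On size, the bias figures rest on assumed rates. The background section describes long waits and scarce psychotherapy in Ontario, so uptake within eight weeks may be low. The model with baseline data and covariates would absorb part of any shift. Every figure in step 4 lies within the ±0.57 SD margin, and the clinical outcomes are exploratory.

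What does not stand is that the matter can be left to a statistical analysis plan. Eligibility and withdrawal rules govern who is followed up, and an analysis plan cannot recover a week-8 outcome that was never collected.

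**Conclusion.** The point holds in a limited form. Criterion 5 is worded on an event that can occur after randomisation, and together with the withdrawal section it permits removal of randomised participants for a reason plausibly related to outcome. It does not require such removal, so the ITT analysis is at risk only if the text is applied literally.

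The firm quantities are 1.7 percentage points of retention per removal, no slack at the expected dropout, and the possible loss of the only post-baseline outcome for each person removed. The size of any bias is unknown. The illustrative shifts of 0.03 to 0.35 SD depend on assumed removal rates, removal from the control arm only, and an assumed link between need for support and outcome. That extra support is likelier among controls, or among those doing worse, is an inference and is not stated in the protocol. The change is worth making because it costs almost nothing and protects both a primary feasibility measure and the effect estimate.

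**What to change.** Reconcile Exclusion Criteria, Concomitant Therapy, Participant Recruitment and Screening, Participant Withdrawal Criteria, Control Group Procedures and the Schedule of Events as follows.

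- Word criterion 5 as an eligibility condition judged at entry: such support ongoing or already planned at that time.
- State that support received after randomisation, already verified at each visit, is recorded by arm as a deviation or intercurrent event. It does not remove anyone from follow-up or from the ITT set, and it may be handled in the per-protocol analysis.
- Separate stopping d-DBT from leaving the study, and collect week-8 outcomes from all randomised participants who have not withdrawn consent.

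Whether such support is discouraged during the study is for the sponsor to decide. These changes concern follow-up and analysis, not the care anyone should receive.

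The cost is a wording amendment, with no change to the planned 60 participants. The downside is that some contamination stays in the ITT estimate, and the record by arm would show how much.

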## Participant Withdrawal Criteria

Participants are advised in the consent form that they are free to withdraw from the study at any time without prejudice and may be withdrawn at the Investigators discretion.

The study participation will also be terminated should participants develop or are found to have any condition that might compromise safety (e.g., unstable vitals). Other reasons for withdrawing individual participants from the study may include one of the following:

- Major protocol violation
- Participant lost to follow-up.
- Withdrawal of consent
- Any participant may be discontinued from the study at the discretion of the investigators if it is deemed to be in the best interest of the participant.

The reason for participant discontinuation or withdrawal from the study will be recorded within the participant’s research record, and/or legal health record.

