## Risks/Benefits

There are no anticipated risks to the participants as the intervention is a ‘light-touch’ psychosocial intervention. It is incumbent upon the research team to identify subjects who require treatment and actively assist them in getting it. Anyone identified with acute psychosis or at acute risk of suicide will be assisted to immediately contact local mental health professionals. If required, the research team will accompany the participant to the local mental health service provider. We have developed a standard operating procedure for risk management that will be adhered to throughout the study. All assessments will be completed in accessible, private, and appropriate venues that suit the needs and preferences of participants. The appointments will be scheduled at times convenient to participants, considering education, household commitments and employment commitments. Participants will not be exposed to a risk of physical and mental harm that is greater than that typically encountered in normal life and the recruitment materials will direct participants to relevant supports if participation raises any concerns. The Digital Navigator will connect with participants weekly, if there are any concerns about risk they will follow our risk management protocol.

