# CLINICAL TRIAL OBJECTIVES

## Specific Aim 1

To adapt an existing, d-DBT intervention for use in young people at CHR for psychosis. **H1:** d-DBT can be clinically adapted and refined in a developmentally appropriate way for virtual use among CHR individuals.

## Specific Aim 2

To evaluate the acceptability of the d-DBT invention and the feasibility of conducting a fully powered randomized controlled trial (RCT) of d-DBT in individuals at CHR for psychosis. **H2:** d-DBT will be acceptable to CHR individuals as demonstrated by qualitative feedback, attendance rates of d-DBT sessions, the Client Satisfaction Questionnaire (CSQ) and the System Usability Scale (SUS). d-DBT for CHR individuals will be feasible as demonstrated by our ability to recruit our desired sample of 60 participants and retain 80% of those recruited by the end of the 8-week study period. Participants’ ability to complete the clinical assessment schedule will also serve as a feasibility indicator.

## Specific Aim 3

To assess the preliminary efficacy of d-DBT in improving functioning and reducing psychiatric comorbidities in individuals at CHR for psychosis in an assessor-masked preliminary RCT clinical trial. **H3**: Individuals with CHR receiving d-DBT will demonstrate enhanced resiliency, reduced depression and anxiety, personality disorder pathology, improved emotional regulation scores, reduced substance use, reduced suicidal ideation, improved functioning and cognitive performance as a result of treatment compared to CHR individuals receiving treatment as usual.

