## Quantitative methods

Assessor-masked pilot RCT comparing the adapted d-DBT intervention to standard outpatient care. Participants in the d-DBT arm will receive the intervention over 8-weeks. Measures will be completed at study entry and repeated immediately post-treatment at 8-weeks. Clinician rated assessments will be completed with a trained research assistant who will be unaware of treatment allocation.

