## Qualitative methods

The sample size for the qualitative component has been determined by the principle of saturation (62); we anticipate that 15 post-intervention interviews will need to be conducted (63). Participants will have the opportunity to consent to the qualitative interview during the initial informed consent discussion at the time of recruitment. The interview would be conducted virtually or in person. We will invite participants who completed the trial and participants who chose to withdraw from the study. Views of the d-DBT intervention, treatment target preferences, and experiences of assessment schedules will be obtained in individual, semi-structured interviews at intervention completion. Interview data will also be collected on usability of the virtual platform, experiences participating remotely/technical experience, overall perception of the program, and barriers/facilitators to participation. An interview guide will be developed from existing literature, together with feedback from the youth advisory group, and will consist of key questions with prompts to enquire further. All interview data will be transcribed verbatim. Data will be analyzed using the five stages of framework analysis (64). Rigor will be ensured by maintaining an audit trail to foster dependability of the process. Confirmability and credibility will be assured by a team approach to data analysis and discussion of the emerging themes. Consensus of the final theoretical framework, reflexivity, and the impact of the researchers on recruitment, data collection and analysis will also be considered (65).

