# PARTICIPANT SELECTION AND WITHDRAWAL

## Target Population

We will recruit 60 CHR participants, with a focus on diversity across genders, ethnic origins, age, and other sociodemographic characteristics. All participants will be assessed at baseline and 8-weeks. We will recruit youth (age 16 – 29 years). The sample size was informed by published literature, which suggests 24-70 participants for pilot trials (83-85).

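### The safety rule ends study participation rather than only d-DBT, and nothing in the protocol keeps the week-8 assessment, the only post-baseline outcome visit, for those participants

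*Protocol*

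**What the plan says.** Participant Withdrawal Criteria sets a mandatory rule: "The study participation will also be terminated should participants develop or are found to have any condition that might compromise safety (e.g., unstable vitals"). The other exits listed there are also withdrawals from the study. The one thing required at exit is that the reason be recorded.

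On outcome timing, Quantitative methods says: "Measures will be completed at study entry and repeated immediately post-treatment at 8-weeks". The Schedule of Events agrees. It has one follow-up visit after the 8-week intervention column, and CSQ-8 and SUS appear only there. Target Population gives a general statement: "All participants will be assessed at baseline and 8-weeks".

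On data after an exit, the only statement is in Participant Recruitment and Screening. It concerns what participants are told about their own right to leave: "they have the option of terminating their participation at any time, without consequence and that no new data will be collected on them".

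Qualitative methods describes who is asked to interview: "We will invite participants who completed the trial and participants who chose to withdraw from the study".

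Statistical Methods plans both ITT and per-protocol/completers-only analyses, and adds: "Full information maximum likelihood approach will be adopted to deal with missing data under the missing-at-random assumption".

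**The concern.** Stopping an intervention for safety and ending outcome collection are different decisions, and the protocol treats them as one. With a single post-baseline visit, a participant terminated before week 8 contributes no post-treatment clinical outcome at all. The measures concerned include the Global Functioning scales, which Statistical Methods names as the efficacy outcome, as well as SIPS and C-SSRS. In the d-DBT arm, CSQ-8 and SUS are lost too, and both are listed among the primary outcomes. A participant whom the study terminates has neither completed nor chosen to withdraw, so the interview invitation does not clearly reach them either.

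The rule is hardest to justify in the treatment-as-usual arm. Those participants receive no study intervention, so ending participation protects them from nothing except the assessments.

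An ITT analysis needs outcomes on everyone randomised wherever they can be obtained. An SAP can choose how to handle missing values, but it cannot recover values that the protocol stopped collecting. The wording therefore belongs in the protocol.

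**Working it through.** **Reading the sections together**

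1. Participant Withdrawal Criteria is the specific rule. It uses mandatory language, covers any condition that might compromise safety, and ends study participation.
2. Target Population says that everyone is assessed at 8 weeks. This is a general schedule and does not mention terminated participants, so it does not clearly override the specific rule.
3. The statement that no new data are collected concerns exits that participants choose. It does not govern safety terminations, though staff could plausibly apply it by analogy.
4. No section provides an early-exit or week-8 assessment after a safety termination. Loss of week-8 data is therefore the plain reading of the rule, but it is not stated.
5. Some information survives: module surveys and weekly check-in data before the exit, the recorded reason, and adverse event follow-up under Safety and Adverse Events.

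**Reproducing the stated margin (Sample Size and Power)**

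Inputs: 30 per arm and about 20% dropout, so 30 × 0.80 = 24 per arm. The half-width of the 95% CI for the standardised difference is 1.96 × √(2/24) = 0.566, which matches the stated ±0.57 SD.

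**Size of the effect on acceptability data**

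Each d-DBT termination removes 1/30 = 3.3% of those randomised to d-DBT from CSQ-8 and SUS, or 1/24 = 4.2% of the 24 expected after dropout.

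**Size of the effect on clinical outcomes**

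The protocol gives no termination rate, so the inputs here are assumptions. Let k of the 30 participants in one arm be terminated, and let their true week-8 scores be d SD worse than the model predicts for them. The arm mean is then off by (k/30) × d.

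| k | d (SD) | Error in arm mean (SD) | Share of ±0.57 SD |
| --- | --- | --- | --- |
| 0 | any | 0 | 0% |
| 1 | 1.0 | 1/30 × 1.0 = 0.033 | 6% |
| 2 | 1.5 | 2/30 × 1.5 = 0.100 | 18% |
| 3 | 1.5 | 3/30 × 1.5 = 0.150 | 26% |

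The error cancels in the group comparison if it is equal in both arms.

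**Size of the effect on precision**

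If three further participants are lost from the expected 48, and the remainder are split evenly at 22.5 per arm, the half-width becomes 1.96 × √(2/22.5) = 0.584 instead of 0.566. This change is negligible.

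**The case against.** The strongest reply is that the protocol never says data collection stops after a safety termination. The no-new-data statement is about voluntary exit, while the general 8-week statement and the planned ITT analysis point the other way. This stands to the extent that the loss is an inference. It does not remove the problem, because nothing tells staff to assess someone whose study participation has been ended.

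The second reply is that the rule may hardly ever operate. Its only example is unstable vitals, and the Schedule of Events contains no vital-signs measurement. The intervention is described as light-touch with no anticipated risks. For the events most likely in this population, Risks/Benefits prescribes referral: "Anyone identified with acute psychosis or at acute risk of suicide will be assisted to immediately contact local mental health professionals". This also stands, and it limits the size of the point.

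A reader might infer that psychiatric worsening will force participants out and so break the missing-at-random assumption. The protocol does not support that as a prediction. It names no psychiatric trigger for termination and directs referral for acute psychosis and suicide risk. The concern about missing-at-random arises only if the broad wording on any condition is applied to such cases.

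A reader might also infer that counting safety exits as losses distorts the retention criterion. Specific Aim 2 sets the target as "retain 80% of those recruited by the end of the 8-week study period", and a participant who leaves for safety reasons is real attrition that a full trial must plan for. The reason for each exit is already recorded, so safety exits can be tabulated apart from voluntary ones.

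Finally, the consent form is not available for this review, and it or the risk-management procedure may already address follow-up after discontinuation. That is possible, but the protocol's own rule should agree with them.

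**Conclusion.** The point holds as a worthwhile, low-cost improvement to the wording. The rule ends study participation where ending d-DBT would be enough, and the protocol does not keep the one post-baseline visit for those affected. No stated figure is wrong, and no direct contradiction is shown.

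The number of terminations is unknown and may be zero. Under the assumed range of one to three terminations in one arm, with scores 1 to 1.5 SD worse than predicted, the error is 0.03 to 0.15 SD. That is small against ±0.57 SD, for outcomes that Statistical Methods calls exploratory. The conclusion rests on the plain reading that ended participation means no week-8 assessment. The documents do not support the firmer claims that week-8 data will certainly be lost, that material bias is likely, or that the retention rate is miscounted.

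**What to change.** Reword Participant Withdrawal Criteria, and the consent form if needed, along these lines: a condition that might compromise safety stops d-DBT where applicable and triggers referral under the procedure in Risks/Benefits. In both arms, the scheduled week-8 assessments (with CSQ-8 and SUS in d-DBT) and adverse event follow-up continue, unless the participant withdraws consent or the investigator judges assessment unsafe. Clinical decisions remain with the investigator.

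Optionally, extend the interview invitation in Qualitative methods to participants discontinued by the investigator.

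The cost is protocol wording and possibly consent wording, with no new visits or measures. Research Visits already allows assessments to be done virtually when possible, although the MCCB needs in-person administration. The small downside is that some participants discontinued for safety are contacted again, at a visit that was already scheduled.
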